## Abstract

**Background:**

After low anterior resection (LAR), up to 90% of patients develop anorectal dysfunction. Especially fecal incontinence has a major impact on the physical, psychological, social, and emotional functioning of the patient but also on the Dutch National Healthcare budget with more than €2000 spent per patient per year. No standardized treatment is available to help these patients. Common treatment nowadays is focused on symptom relief, consisting of lifestyle advices and pharmacotherapy with bulking agents or antidiarrheal medication. Another possibility is pelvic floor rehabilitation (PFR), which is one of the most important treatments for fecal incontinence in general, with success rates of 50–80%. No strong evidence is available for the use of PFR after LAR. This study aims to prove a beneficial effect of PFR on fecal incontinence, quality of life, and costs in rectal cancer patients after sphincter-saving surgery compared to standard treatment.

**Methods:**

The FORCE trial is a multicenter, two-armed, randomized clinical trial. All patients that underwent LAR are recruited from the participating hospitals and randomized for either standard treatment or a standardized PFR program. A total of 128 patients should be randomized. Optimal blinding is not possible. Stratification will be done in variable blocks (gender and additional radiotherapy). The primary endpoint is the Wexner incontinence score; secondary endpoints are health-related and fecal-incontinence-related QoL and cost-effectiveness. Baseline measurements take place before randomization. The primary endpoint is measured 3 months after the start of the intervention, with a 1-year follow-up for sustainability research purposes.

**Discussion:**

The results of this study may substantially improve postoperative care for patients with fecal incontinence or anorectal dysfunction after LAR. This section provides insight in the decisions that were made in the organization of this trial.

**Trial registration:**

Netherlands Trial Registration, NTR5469, registered on 03-09-2015.

Protocol FORCE trial V18, 19-09-2019.

Sponsor Radboud University Medical Center, Nijmegen.

## Background

The treatment of rectal cancer has improved greatly over recent years in terms of oncological outcomes. Combinations of surgery, radiotherapy and/or chemotherapy are responsible for improved survival data. Nowadays most of these patients can be treated with a sphincter-saving technique, such as the low anterior resection (LAR). Unfortunately, the majority of these patients develop anorectal dysfunction [1], which can consist of urgency, increased frequency of defecation, fecal incontinence, soiling, no control on flatus or incomplete evacuation. Up to 76–90% of these patients report a combination of these complaints, which are described as low anterior resection syndrome (LARS) [2, 3]. Fecal incontinence especially has a major [1, 4, 5] impact on the physical, psychological, social, and emotional functioning of the patient [3, 6].

Alongside the impact on personal life, fecal incontinence has a substantial impact on the National Healthcare budget with more than € 2000 spent per patient per year in the Netherlands [7]. Production losses in paid and unpaid work accounted for more than half of the total costs, and costs of healthcare visits accounted for almost a fifth of the total costs. One-tenth of the total cost is associated with protective material (only partially reimbursable), while incontinence medication was only responsible for 5% of the total costs [7]. Currently, the exact prevalence of LARS in the Netherlands is unknown, but an increase in the numbers of patients suffering LARS in the Netherlands is expected due to the start of colorectal cancer screening in January 2014 among men and women between 55 and 75 years.

Despite the large impact of LARS, no gold standard exists to treat these patients in a way that focuses on the cause of the problem. The current standard treatment is focused on symptom relief, consisting of pharmacotherapy with bulking agents and/or anti-diarrheal medication. However, no sustained clinical improvements of these therapies in LARS patients have been reported. Pelvic floor rehabilitation (PFR) is one of the most important treatments for fecal incontinence in general, with success rates of 50–80% [8–10]. Based on previous studies, we hypothesize that PFR might reduce the number and severity of fecal incontinence after rectal resections by 25% (measured by the Wexner score) [11–15].

The FORCE trial randomizes rectal cancer patients after sphincter-saving rectal resection for either a standardized pelvic floor rehabilitation program or standard treatment to investigate which arm results in a greater decrease of complaints and costs of fecal incontinence.

## Methods/Design

### Study design and research questions

The FORCE trial is a multicenter, two-armed, randomized controlled trial. The severity of fecal incontinence (FI) in patients after LAR will be measured by the Wexner score. Secondary study objectives are to determine the effect of PFR compared to standard treatment on the quality of life (by measuring the fecal incontinence quality of life and using the EORTC Colorectal Quality of Life Questionnaire QLQ-CR29), to analyze the cost effectiveness of full implementation of PFR compared to present daily practice (standard treatment) in treating and preventing functional bowel complaints in patients after LAR. In addition, this study aims to explore the effect of demographic, surgical and oncologic parameters on the development of FI after LAR relative to PFR and standard treatment.

### Study population

The study population consists of rectal cancer patients living in the Netherlands who undergo sphincter saving surgery (low anterior resection, LAR) in one of the participating hospitals (*n* = 17): Radboud University Medical Center Nijmegen, University Medical Center Groningen (UMCG), Medical Center Leeuwarden (MCL), Isala Clinics Zwolle, Antonius Hospital Sneek, Nij Smellinghe Drachten, Ommelander Hospital Groningen (OZG), Canisius-Wilhelmina Hospital (CWZ) Nijmegen, Deventer Hospital, Slingeland Hospital Doetinchem, Máxima MC (MMC) Veldhoven/Eindhoven, Treant Zorggroep Emmen, Bernhoven Uden, Tjongerschans Heerenveen, Elizabeth TweeSteden Ziekenhuis (ETZ) Tilburg, Maasziekenhuis Pantein Boxmeer, and Streekziekenhuis Koningin Beatrix (SKB) Winterswijk. In each center, a principal investigator is assigned for inclusion and informed consent (Additional file 1). In case of a temporary stoma, patients can participate until 6 weeks after closure. Without a temporary stoma, patients can participate 3 months after closure. Inclusion criteria are (1) adults (≥18 years), (2) LAR for rectal carcinoma, and (3) being intellectually and/or linguistically capable of understanding the questionnaires. Patients with a history of proctitis, colitis ulcerosa, or Crohn’s disease; a life expectancy of less than 1 year; and mental or physical inabilities to undergo PFR are excluded. Participants with locally advanced (T4) tumors indicated for extensive resection (beyond TME) and patients who received invasive physiotherapy during the previous 6 months are excluded as well.

### Flow of the FORCE trial

After surgery, eligible patients will be randomized for either a standardized pelvic floor rehabilitation (PFR) program or standard treatment, which is defined as current daily practice. Blinding for PFR is not possible. Randomization and data collection will be performed by the coordinating investigator. In concordance with the study flowchart (Fig. 1), these steps will be followed:
After giving informed consent, eligible patients will be included in the FORCE trial. In the beginning of the inclusion period, this inclusion was supposed to occur preoperatively with a baseline measurement before surgery as well (measurement 1, M1). Since this preoperative inclusion led to reduced numbers of inclusion due to an overload of information, postoperative inclusion was allowed as well.Questionnaires will be administered 3 months after LAR (measurement 2, M2) to patients without a temporary stoma. Based on the current reports, approximately 70% of patients undergoing LAR also receive a temporary stoma [16]. In these cases, the questionnaires will be administered 6 weeks after stoma closure (measurement 2, M2).Randomization will take place after completing the M2 questionnaires. Patients will then undergo either standard treatment or a standardized PFR program that includes the standard treatment for 3 months (12 sessions, once a week).After finishing the PFR program or 12 weeks of participation in the control group, questionnaires will be send again (measurement 3, M3, primary endpoint).Long-term follow-up will be completed at 1 year after bowel continuity (measurement 4, M4).

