**Fig. 1 Fig1:**
[figure not shown]
Flowchart of the FORCE trial. Abbreviations: M1–4, measurement 1 till 4. LAR, low anterior resection

Patients who decline the request for participation will be asked to fill out the DeFeC questionnaire (with Wexner score included) and LARS score only one time. These patients will sign a separate informed consent form for this step (Additional file 2). Study participation for these patients will stop directly after finishing these questionnaires. By means of this questionnaire, a valid statement can be made about the potential selection bias for participation that is based on the amount of complaints.

Patients from the control group who would like to undergo PFR will be given the opportunity to undergo this treatment after finishing measurement 3 (M3). These patients will undergo an identical PFR program as the patients that are initially randomized to this intervention and will be asked to fill in another questionnaire (similar to M2/M3) after their treatment. This might provide useful information about whether the timing of PFR is of influence on the results.

This study protocol is in accordance with the 2013 Standard Protocol Items: Recommendations for Interventional Trials (SPIRIT) Statement [17]. The checklist can be found in Additional file 3. The schedule of enrollment, interventions, and assessments is shown in Table 1.

**Table 1 Tab1:** The schedule of enrollment, interventions, and assessments (according to the SPIRIT statement 2013)

TIME POINT		STUDY PERIOD				
	Enrollment	Allocation^a^	Post-allocation			Close-out
	October 2017 – December 2019	0	t_1_^b^	t_2_^b^	t_3_^b^	December 2019 – June 2020.
ENROLLMENT:						
Eligibility screen	X					
Informed consent	X					
Randomization and allocation		X				
INTERVENTIONS:						
Pelvic Floor Rehabilitation			X			
Control group			X			
ASSESSMENTS:						
Questionnaires to assess study outcomes			X	X	X	
Statistical analysis						X

^a^Allocation of the intervention/control group takes place 3 months after index surgery without temporary stoma construction or 6 weeks after stoma reversal if initial surgery included stoma construction. Measurement t1 will always take place before randomization/allocation

^b^*t1* measurement before randomization, *t2* primary endpoint (12 weeks after control/intervention period), *t3* one year follow-up

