### Data analysis and statistics

#### Primary outcome

The primary outcome is based on the Wexner score. The dependent variable is the severity of FI measured by this score. The independent variable is the intervention or the standard treatment. The difference between the intervention and control group will be analyzed by an analysis of covariance (ANCOVA), with the baseline measurement as covariate. This test is preferred over the T-test since this analysis reduces the within-group error variance. Therefore, the precision of the treatment estimate is increased, and the length of the confidence interval is reduced [18]. The M3 measurement will be valid as the primary outcome. The M4 measurement, which is used to assess sustainability of results, will be influenced by the patients of the control group who will choose to undergo PFR after finishing their primary endpoint measurements (after 3 months of standard treatment, i.e., in case of severe FI). For statistical analysis, the effect between the intervention group and control group will be evaluated with and without this group to measure the influence of this group on the M4 measurement. The same analysis of covariance (ANCOVA) will be used.

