#### Handling and storage of data and documents

The anonymized data will be stored in Castor EDC. Only the coordinating and principal investigators will have access to the key of the code that matches participants to study data. Most patients will fill in their questionnaires themselves online. Only those without email will fill in the paper version of the questionnaires.

No specific plans, besides an active attitude towards the participating centrums, are made to promote participant retention and complete follow-up. If patients fail to start/continue their allocated intervention (Pelvic Floor Rehabilitation, since failure of control group is not possible), data will be collected according to the study protocol for use in per protocol analysis.

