#### Pelvic floor muscle training

Patients will start with the intervention trajectory 3 months after LAR or 6 weeks after stoma closure. During the next 3 months, they will undergo 12 treatment sessions, once per week. The first session will take 45 min, and the following sessions 30–35 min. During every treatment, the physiotherapist will complete a case report form. This case report form contains all information concerning pelvic floor muscle training, biofeedback, electrostimulation, peri-anal examination, and digital rectal examination. Digital rectal examination of pelvic floor functionality will be used to assess the ability to consciously contract the pelvic floor muscles and to quantify the strength of the contraction [8, 32]. The use of medication according the standard treatment will be reported also in the case report form. All patients randomized to the intervention group will be instructed by their physiotherapist on how to exercise the pelvic floor. The patients will be thought to selectively generate voluntary contractions of the puborectal muscle and the external anal sphincter and also how to relax these muscles and to avoid co-contractions of other muscles. The pelvic floor has to satisfy requirements of maximal strength, progression of the duration of the strength, and progression in timing and coordination of the contraction [8, 32]. Additionally, folders will be provided, with illustrations and short descriptions of exercises, which have to be performed at home three times per day, preferably at fixed time points [8, 32]. The success of PFR depends greatly on the motivation, willingness, and self-discipline of patients to exercise at home [8, 32].

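### The primary endpoint M3 is tied to programme completion in the PFR arm and to 12 weeks in the control arm, its timing is worded inconsistently, and patients who stop PFR have no dated M3

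*Protocol article*

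**What the plan says.** All references are to the protocol article.

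- **Primary outcome** makes M3 the primary time point: "The M3 measurement will be valid as the primary outcome".
- **Flow of the FORCE trial** sets the rule by arm: "After finishing the PFR program or 12 weeks of participation in the control group, questionnaires will be send again". M4, by contrast, has one clock for everyone, one year from restored bowel continuity.
- **Abstract, Methods** counts from the intervention: "The primary endpoint is measured 3 months after the start of the intervention".
- **Table 1, footnote b** defines t2 as "primary endpoint (12 weeks after control/intervention period".
- **Primary outcome** also implies a time for controls. Those who opt for PFR do so "after finishing their primary endpoint measurements (after 3 months of standard treatment, i.e., in case of severe FI".
- **Pelvic floor muscle training** gives the planned course: "Patients will start with the intervention trajectory 3 months after LAR or 6 weeks after stoma closure", and then "During the next 3 months, they will undergo 12 treatment sessions, once per week". Randomisation has the same nominal date.
- **Handling and storage of data and documents** covers patients who do not start or continue PFR: "data will be collected according to the study protocol for use in per protocol analysis".
- **Intention to treat and per protocol analysis** bases the primary outcome on intention to treat, with per protocol as an addition.

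**The concern.** A primary endpoint should be measured at the same time since randomisation in both arms. Here one arm is timed by the calendar and the other by an event that depends on treatment. Randomisation falls 3 months after surgery or 6 weeks after stoma closure, when bowel function may still be changing without PFR. The protocol itself wants to learn whether the timing of PFR after surgery influences results. If M3 slips in the PFR arm only, any spontaneous recovery in the gap counts as a PFR effect.

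Slippage is plausible. The physiotherapist is informed of the referral only after randomisation, treatment takes place in hospital-based or private practices, and the protocol calls adherence a common problem.

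The literal footnote would change the question from effect at the end of treatment to persistence 12 weeks later. It would also separate two statements that otherwise agree. The flow section opens PFR to controls after M3, while the control group section opens it after the control period. With M3 at week 24, controls could have had PFR before the primary endpoint.

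Patients who do not finish PFR are the ones an intention-to-treat analysis must keep, and the flow rule gives them no date.

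**Working it through.** **1. M3 in weeks from randomisation.** The clock for control participation is taken to start at randomisation. Let d be the delay from randomisation to the first PFR session and m the number of missed or postponed weeks. Twelve weekly sessions span 12 − 1 = 11 weeks from first to last.

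| Source | Arm | Time of M3 |
|---|---|---|
| Flow section | Control | 12 |
| Flow section | PFR | d + 11 + m |
| Abstract | Counted from start of intervention | 3 × 52/12 = 13 (plus d in the PFR arm) |
| Primary outcome section | Control | about 13 (3 months) |
| Table 1 footnote b, literal | Both | 12 + 12 = 24 |

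With d = m = 0, all sources except the footnote fall between weeks 11 and 13. Only the footnote stands apart, by about 12 weeks.

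**2. Gap between arms under the flow rule.**

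Gap = (d + 11 + m) − 12 = d + m − 1 weeks.

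On plan the gap is −1 week, so PFR is measured slightly earlier. Once d + m exceeds 1 week, PFR is measured later. The documents give no value for d or m.

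**3. Bias from the gap.** Bias = recovery slope × gap ÷ (52/12), with the slope in Wexner points per month and the gap in weeks. The documents give no slope, so 0.1 to 1.0 points per month is an assumption.

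| Gap (weeks) | Slope 0.1 | Slope 1.0 | Share of 5-point target |
|---|---|---|---|
| −1 | 0.02 against PFR | 0.23 against PFR | 0.5–5% |
| 2 | 0.05 for PFR | 0.46 for PFR | 1–9% |
| 4 | 0.09 for PFR | 0.92 for PFR | 2–18% |
| 8 | 0.18 for PFR | 1.85 for PFR | 4–37% |

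Example: 1.0 × 8 ÷ 4.33 = 1.85 points, and 1.85/5 = 37%.

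**4. Patients who do not start or continue PFR.** The flow rule sends M3 when the programme is finished, and these patients do not finish it. The data-handling section says their data are collected as the protocol prescribes, which leads back to the flow rule and supplies no date. It then names the per-protocol analysis as the use of these data, whereas the primary analysis is intention to treat. The number affected is not given. The sample size section allows for 50% withdrawal or replacement, so it need not be small.

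**5. Effect on sample size.** None. The stated 32 evaluable per arm and 128 randomised (32 ÷ 0.5 × 2) do not depend on how M3 is dated.

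**The case against.** The strongest case on the other side is that this is a matter of wording. The flow, abstract, primary outcome and muscle-training sections all describe about 3 months. The primary outcome section rules out week 24 for controls, so the footnote is most likely loose phrasing for the end of the 12-week period. Measuring at the end of treatment is a defensible choice, and a journal article may leave visit windows to the full protocol.

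The likely bias is also modest against sampling error. With SD 8, R = 0.5 and 32 per arm, the standard error is 8 × √0.75 × √(2/32) = 1.73 points. A 4-week gap at 0.25 to 0.5 points per month gives 0.23 to 0.46 points, or 0.13 to 0.27 standard errors.

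Most of this stands, and it rules out three stronger readings that a reader might infer:

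- *That there are three or four conflicting definitions.* The sections other than the footnote differ in anchor but agree on plan.
- *That PFR patients are measured later.* No waiting time, missed-session rate or overrun is given, and on plan they are measured about a week earlier. Later measurement is a risk and not a feature of the design.
- *That patients who stop PFR never get an M3.* The data-handling section states that their data are still collected.

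The objection does not remove the arm-dependent rule, the footnote's place in the schedule of assessments, or the missing date and misassigned analysis for patients who stop PFR. The absence of a window in the article is not itself counted as a defect.

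**Conclusion.** The point holds in limited form. The primary endpoint's timing rule depends on arm, Table 1 footnote b conflicts with the other sections by about 12 weeks if taken literally, and patients who do not complete PFR have no dated M3 while their data are earmarked for the wrong analysis.

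The size of any timing bias cannot be estimated from the documents. The range of 0.05 to 1.85 Wexner points in favour of PFR rests wholly on assumed slopes (0.1 to 1.0 points per month) and assumed gaps (2 to 8 weeks). If PFR runs exactly to plan, the sign reverses and the bias is 0.02 to 0.23 points. The case for a change rests on the rule itself. The trial is open label with a patient-reported endpoint, and the coordinating investigator who collects the data knows the allocation, so the time of M3 should leave no room for discretion.

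**What to change.** 1. Define M3 in the abstract, the flow section and Table 1 footnote b as one fixed time from randomisation, the same in both arms, with a stated window.
2. Send M3 to every randomised patient at that time, whether or not PFR was started, continued or completed.
3. State in the data-handling section that data from patients who do not start or stop PFR enter the intention-to-treat analysis. They may also inform the per-protocol analysis.
4. Reconcile the two statements on when controls may receive PFR (after M3, or after the control period) with the M3 definition.
5. For patients already measured, report the randomisation-to-M3 interval by arm and add a sensitivity analysis restricted to in-window measurements. This restriction selects on something that happens after randomisation, so it should support the primary intention-to-treat result and not replace it.

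The cost is a short amendment and a change in when the questionnaire goes out. Recruitment was still open at submission, so later patients can follow the new rule. The sample size stays at 32 evaluable per arm and 128 randomised. The downside is that some PFR patients will have had fewer than 12 sessions at M3, so the estimate becomes the effect of being assigned to PFR at a fixed time and not the effect at programme completion.
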